## Abstract

**Introduction::**

Poststroke depression is a serious and common complication of stroke, especially the ischemic poststroke depression. Antidepressants are used in poststroke depression, and acupuncture may be an alternative approach. However, the efficacy and mechanism of acupuncture for poststroke depression has not been confirmed.

**Methods/design::**

This is a multicenter, central-randomized, single-blind, sham-controlled clinical trial. We will allocate 208 subjects aged between 40 and 80 years old, diagnosed with initial poststroke depression (PSD) within 6 months to 2 groups randomly in a ratio of 1:1. Patients in the experimental group will be treated with traditional acupuncture and placebo pills, whereas the others in the control group will be treated with sham-acupoints acupuncture and antidepressant (fluoxetine hydrochloride tablets). All will be given acupuncture and/or medication treatment for 12 weeks, and then received 12-week follow-up. Patients will be evaluated with the 17-item Hamilton Depression Scale and Se1f-rating Depression Scale for depression state, National Institute of Health Stroke Scale for neurological deficit, Modified Barthel Index for activities of daily living, Treatment Emergent Symptom Scale for side effects of treatments, diagnosis and evaluation criteria of traditional Chinese medicine for stroke (try out) for curative effects of stroke, and clinical global impression for synthesize effect before and the 2nd, 4th, 8th, and 12th week of treatment, 24th week of follow-up. Study on mechanisms of acupuncture will be revealed through the diversity of brain metabolites (choline-containing compounds [Cho], N-acetylaspartate [NAA], myoinositol, glutamine and glutamate complex, creatine [Cr], Cho/Cr, Cho/NAA, Cr/NAA) in bilateral dorsolateral prefrontal cortex and anterior cingulate cortex monitored by proton magnetic resonance spectroscopy, and serum monoamine neurotransmitters (5-hydroxytryptamine, norepinephrine, dopamine) and cytokines (brain-derived neurotrophic factor [BDNF], interleukin [IL]-4, IL-6, IL-10, IL-18, IL-1β, tumor necrosis factor alpha) before and the 12th week of treatment. Baseline characteristics of patients will be summarized by groups and compared with chi-square for categorical variables, and 2-sample *t* tests or Wilcoxon rank-sum test for the continuous variables. Primary and secondary outcomes according to the measurement times are applicable to univariate repetitive measurement deviation analysis or 2-sample *t* tests, or Wilcoxon rank-sum test.

**Conclusion::**

The present research is designed to investigate efficacy and mechanism of traditional acupuncture therapy on ischemic PSD, also to explore the correlation between cerebra metabolic and serologic factors, and ischemic PSD. With this research, we are looking forward to find out an appropriate alternative nondrug therapy for PSD people to alleviate the adverse effects and drug dependence caused by antidepressants.

## Introduction

1

Poststroke depression (PSD) is a serious and common complication of stroke.^[1]^ Reports revealed that the prevalence of PSD was from 30% to 65%.^[2,3]^ PSD has been associated negatively with survival, cost of medical care, and compliance with therapy including rehabilitation, functional outcome, resumption of social activities, and quality of life.^[4]^

At present, the treatment of PSD mostly applies selective serotonin reuptake inhibitors (SSRIs). A meta-analysis of randomized controlled trials for PSD has revealed that patients in the SSRIs group had make great improvement in depressive symptoms significantly compared with the placebo group.^[5]^ Several controlled studies have demonstrated that while some patients made improvement on depression scores significantly, others discontinued due to side effects.^[6,7]^ And SSRIs have slow onset speed about 3 to 4weeks.^[5]^ A trial suggested that the advantages of fluoxetine hydrochloride could not be demonstrated within the first 3 months compared with controlled treatment.^[8]^ On the contrary, the use of antidepressants might also increase the risk of interactions derived from various drugs, as most stroke patients concurrently take.^[9]^

Acupuncture is 1 of the main treatments of traditional Chinese medicine (TCM) which has been used for over 2000 years. Acupuncture is widely used in the treatment of PSD. A meta-analysis has demonstrated that the curative effect of acupuncture on PSD was superior to antidepressants among waitlist controls in improving both response and symptom severity.^[10]^ Another meta-analysis revealed that there is no difference in effective rate on comparison between the acupuncture group and western medicine group in treating PSD.^[11]^

In China, because of the good effect, more and more patients are willing to choose acupuncture for PSD. However, no sufficient clinical trial data and solid evidence could confirm whether acupuncture could yield certain efficiency in treating PSD and how acupuncture works. It is necessary to verify the effectiveness and mechanism of acupuncture from senior quality studies. Now, the evidence about acupuncture effect on treating PSD is inadequate and must apply further strictly design clinical studies.

The primary objectives of this study are to evaluate the efficacy and mechanism of acupuncture treatment and follow-up on PSD during 6 months.

## Methods/design

2

### Study design

2.1

This is a multicenter, central-randomized, single-blind, sham-controlled, noninferiority clinical trial. In all, 208 participants will be randomized into 2 groups at a ratio of 1:1. Participants in the treatment group will be treated with traditional acupuncture and placebo medicine. Participants in the control group will be treated with sham-acupoint acupuncture and medicine (fluoxetine hydrochloride tablets).

The whole study period is 25 weeks, including 1-week baseline observation, 12-week treatment, and 12-week follow-up. Patients will be evaluated with scales for clinical efficacy before and the 2nd, 4th, 8th, 12th week of treatment, and 24th week of follow-up, and monitored by proton magnetic resonance spectroscopy (^1^H-MRS) and serum for acupuncture mechanisms before and the 12th week of treatment (Fig. 1).

**Figure 1 F1:**
[figure not shown]
Study design and participant flow chart.

The clinical trial results will be reported according to the Standards for Reporting Interventions in Clinical Trials of Acupuncture (STRICTA) statement.^[12]^

### Ethics

2.2

This study has been approved by the ethics committee of First Teaching Hospital of Tianjin University of Traditional Chinese Medicine, and registered on *ClinicalTrials.gov* with the ID NCT02472613. Informed consents will be obtained from all the subjects involved.

### Study population

2.3

#### Inclusion criteria

2.3.1

The inclusion criteria are as follows:

1.Subjects diagnosed with ischemic stroke in International Classification of Diseases (ICD-10-I63.902).^[13]^2.Subjects diagnosed with secondary mild and moderate-grade depression, 17-item Hamilton Depression Scale (HAMD-17) scores between 7 and 24 points^[14]^, according to the Diagnostic and Statistical Manual of Mental Disorders-Fourth Edition (DSM-IV) or Chinese Classification and Diagnostic Criteria of Mental Disorders-Third Edition (CCMD-III).^[15,16]^3.Subjects aged between 40 and 80 years old, male or female.4.Subjects diagnosed with depression for the first time after ischemic stroke.5.Subjects diagnosed with initial PSD within 6 months.6.Cooperation during examination, without aphasia and severe cognitive disorders, Mini-Mental State Examination (MMSE) scores >17 points^[17]^.

#### Exclusion criteria

2.3.2

The exclusion criteria are as follows:

1.Subjects diagnosed with primary depression or secondary major depressive disorder, HAMD-17 scores >24 points^[14]^.2.Participation in any other clinical trial or taking antidepressants in recent 2 weeks.3.With aphasia and severe cognitive dysfunction (MMSE scores <17 points).^[17]^4.With severe heart disease, malignancy, kidney, and liver function insufficiency.5.Pregnant or lactating women.

### Study settings and recruitments

2.4

The present study will be conducted in the following 3 hospitals: First Teaching Hospital of Tianjin University of Traditional Chinese Medicine, Beijing Hospital of Traditional Chinese Medicine of Capital Medical University, Tianjin Academy of Traditional Chinese Medicine Affiliated Hospital, and Second Affiliated Hospital of Anhui University of Traditional Chinese Medicine (later joined).

Participants with the diagnosis of ischemic stroke with depression will be recruited at the above mentioned 4 hospitals, who mainly come from hospital wards and clinics. Apart from this, posters, leaflets, and the routine-free clinics will also be helpful. Sure, except these, the hospital websites, WeChat, and Microblogging are powerful advocacy media.

### Study group

2.5

In all, 208 subjects who meet the criteria with informed consents will be selected. The subjects will be randomly divided into 2 groups, namely the experimental group and control group, 104 cases in each group.

### Study time

2.6

This clinical study was conducted from May, 2016 to June, 2018. It is expected that all subjects’ follow-up observation will end in the second half of 2019 because of the delayed recruitment.

### Interventions

2.7

Interventions were selected based on the theory of TCM and expert-level discussions. The acupuncturists involved have received their practitioners’ license from China's National Health and Family Planning Commission, who have worked for more than eight years. Subjects in experimental group received verum acunpuncture and placebo pills, and others in control group received sham-acupionts acunpuncture and medications. Apart from this, the regular drugs used in neurological department are allowed, such as antihypertensive drugs, lipid-regulating drugs, and antiplatelet drugs.

#### Experimental group

2.7.1

##### Verum acupuncture

2.7.1.1

Disposable sterile acupuncture needles (0.25 × 40 mm; Hwato Brand, Suzhou Medical Supplies Factory Co., Ltd., Suzhou, China) were used. “*Tiaoshen-Kaiqiao*” acupuncture is applied to treat PSD according to TCM theory. Acupoints are including bilateral PC6 (*Neiguan*), GV26 (*Shuigou*), EX-HN3 (*Yintang*), GV23 (*Shangxing*), GV20 (*Baihui*), EX-HN1 (*Sishencong*), bilateral ST2 (*Sibai*), bilateral GB20 (*Fengchi*), and affected side LI15 (*Jianyu*), LI11 (*Quchi*), LI10 (*Shousanli*), LI4 (*Hegu*), GB31 (*Fengshi*), SP10 (*Xuehai*), ST36 (*Zusanli*), SP6 (*Sanyinjiao*) and LR3 (*Taichong*).

Acupoints GV26, GV23, GV20, ST2, and EX-HN1 are inserted at the depth of 5 to 10 mm, whereas others are inserted at the depth of 20 to 30 mm. Then pecking-acupuncture technique is done on GV26 to achieve strong stimulation for 6 to 9 seconds. Lifting-thrusting and twirling-rotating manipulations are conducted on others for called “*De Qi*” sensation, like the feeling of soreness, numbness, heaviness, and distension. Finally, all needles would be removed after retained for 30 minutes. Participants will be treated 3 sessions per week for 12 consecutive weeks.

##### Placebo pills

2.7.1.2

Ingredients of the placebo pills are starch produced by TIPR Pharmaceutical Co., Ltd, which exactly have the same shape and taste as fluoxetine hydrochloride tablets. Two tablets each time, one time a day for 12 weeks.

#### Control group

2.7.2

##### Sham-acupoints acupuncture

2.7.2.1

Sham-acupoints acupuncture mainly consists of some sham-acupoints, which have no therapeutic effect on depression in light of literatures^[18]^ and clinical experience, such as SJ14 (*Jianliao*), PC2 (*Tianquan*), LU4 (*Xiabai*), SJ12 (*Xiaoluo*), LI13 (*Shouwuli*), SJ9 (*Sidu*), SJ7 (*Huizong*), LI7 (*Wenliu*), LI12 (*Zhouliao*), PC3 (*Quze*), LI6 (*Kongzui*), SJ6 (*Zhigou*), SJ3 (*Zhongzhu*), ST32 (*Futu*), SP11 (*Jimen*), ST33 (*Yinshi*), ST34 (*Liangqiu*), ST37 (*Shangjuxu*), ST39 (*Xiajuxu*), GB33 (*Xiyangguan*), LR5 (*Ligou*), BL61 (*Pucan*), BL64 (*Jinggu*), KI2 (*Rangu*), LR5 (*Ligou*), ST44 (*Neiting*) on the affected side upper and lower extremities. Manipulators should choose aboved acupionts in accordance with verum acupuncture group about the number of acupoints and the stimulating amount of acupuncture, whereas, without “*De Qi*” sensation. The rest are the same as the verum acupuncture group.

##### Fluoxetine hydrochloride

2.7.2.2

Fluoxetine hydrochloride tablets (10 mg per tablet; Changzhou Siyao Pharmaceutical Co., Ltd., Changzhou, China) as a SSRI are used. Two tablets each time, one time a day for 12 weeks.

### Adverse events observation

2.8

It could be that patients with subcutaneous bleeding or hematoma, needle sickness, and pain around acupionts at needling are more likely related to acupuncture. Sickness, vomiting, diarrhea, headache, anxiety, insomnia, drowsiness, fatigue, sweating, tremors, and skin rash occur in patients are probably connected to drugs. With the Treatment Emergent Symptom Scale (TESS) and patients’ diary, all adverse events are to be recorded and measured during treatment and the follow-up period. Serious adverse events should be reported to the principal investigator immediately. All details will be documented, appropriate medical care will be given at once.

### Primary outcomes

2.9

The HAMD-17 and Se1f-rating Depression Scale (SDS)^[19]^ scores for depression state before and the 2nd, 4th, 8th, 12th week of treatment, and 24th week of follow-up. The diversity of choline-containing compounds (Cho), N-acetylaspartate (NAA), myoinositol (MI), glutamine and glutamate complex (Glx), creatine (Cr), Cho/Cr, Cho/NAA, and Cr/NAA in bilateral dorsolateral prefrontal cortex and anterior cingulate cortex. The levels of 5-hydroxytryptamine (5-HT), norepinephrine (NE), dopamine (DA), brain-derived neurotrophic factor (BDNF), intereukin (IL)-4, IL-6, IL-10, IL-18, IL-1β, and tumor necrosis factor alpha (TNF-α) in serum before and the 12th week of treatment.

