### Estimation of sample size

2.11

Based on the previous pilot study,^[25]^ the mean change in HAMD-17 before and after treatment was used as the indicator for the efficacy evaluation in the calculation of the sample size. Results from our previous studies showed that the mean HAMD-17 scores change was 10.49 ± 4.55 after acupuncture treatment and 10.24 ± 4.46 after fluoxetine treatment. Thus, we performed a noninferiority test to calculate the appropriate trial sample size with 90% power, beta of 0.1, alpha of 0.05. The results showed that a clinically important difference can be detected by a sample size of at least 84 in each group. This number was then increased to 104 per group to allow a predicted 20% dropout rate. We will plan to enroll in all 208 participants in this study.

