### Statistical analysis

2.13

Data analysis will be based on intention-to-treat analysis (ITT) and/or per-protocol analysis (PP) principle in the light of missing data. We will also evaluate the group effect by comparing the analysis results between the above 2 data sets to evaluate robustness of our analytical results.

All data will be analyzed using SPSS19.0 (v19.0, SPSS Inc., Chicago, IL) in the China Academy of Chinese Medical Sciences (CACMS). A *P* value <.05 will be considered as significant. Descriptive statistics will be performed with mean, standard deviation (SD), maximum, minimum, and so on by groups and time.

Baseline characteristics of patients will be summarized by groups and compared with chi-square for categorical variables, and 2-sample *t* tests (normal distributions) or Wilcoxon rank-sum test (non-normal distributions) for the continuous variables. Primary and secondary outcomes according to the measurement times are applicable to univariate repetitive measurement deviation analysis or 2-sample *t* tests, or Wilcoxon rank-sum test. If there is a violation of distribution assumption, appropriate transformation will be used.

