#### Primary outcomes

2.13.1

We will use univariate repetitive measurement deviation analysis with HAMD-17 and SDS scores before and the 2nd, 4th, 8th, 12th week of treatment, and 24th week of follow-up as the outcomes. A significant effect of group indicates that the HAMD-17 and SDS scores are different between groups after interventions.

The diversity of Cho, NAA, MI, Glx, Cr, Cho/Cr, Cho/NAA, and Cr/NAA will be compared with 2-sample *t* tests or Wilcoxon rank-sum test with their concentrations or ratios before and the 12th week of treatment as the outcome variables. Similar analysis approach will be used for the levels of 5-HT, NE, DA, BDNF, IL-4, IL-6, IL-10, IL-18, IL-1β, and TNF-α in serum.

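### Section 2.9 makes 20 measures (36 to 44 if each brain region is tested) primary, each judged at P<.05, while the trial is sized on HAMD-17 change alone; a chance-significant primary result is likely

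*Protocol article*

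**What the plan says.** Section 2.9 of the protocol article (Primary outcomes) names HAMD-17 and SDS, then eight spectroscopy quantities (five metabolites and three ratios formed from them), then ten serum markers. The imaging regions and the first serum markers follow one another directly: "in bilateral dorsolateral prefrontal cortex and anterior cingulate cortex. The levels of 5-hydroxytryptamine (5-HT), norepinephrine (NE), dopamine (DA", and so on through the cytokines. All carry the same status.

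Section 2.13.1, also headed as primary outcomes, gives each type a between-group test:
- Scales: "We will use univariate repetitive measurement deviation analysis with HAMD-17 and SDS scores before and the 2nd, 4th, 8th, 12th week of treatment", and again at week 24.
- Spectroscopy: "The diversity of Cho, NAA, MI, Glx, Cr, Cho/Cr, Cho/NAA, and Cr/NAA will be compared with 2-sample" t tests or rank-sum tests.
- Serum: "Similar analysis approach will be used for the levels of 5-HT, NE, DA, BDNF, IL-4, IL-6, IL-10, IL-18, IL-1β, and TNF-α in serum".

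Section 2.13 gives a single decision rule, that a P "value <.05 will be considered as significant". Section 2.11 bases the sample size on one variable: "the mean change in HAMD-17 before and after treatment was used as the indicator for the efficacy evaluation in the calculation of the sample size".

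**The concern.** A primary outcome is the one on which the trial's conclusion rests. Here dozens of variables share that status and one per-test threshold, and only one of them was used for sizing. Two things are at stake.

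First, a single nominally significant metabolite or cytokine could be reported as a positive primary finding and as evidence of mechanism, when chance alone would often produce one. Second, HAMD-17 and SDS are both primary for efficacy, and the article does not say which decides if they point in different directions.

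This is not a detail left to an analysis plan that is not shown. The article itself fixes the list and the threshold. A later plan could add an adjustment, but section 2.9 would still name all of these as primary.

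**Working it through.** **The plan's own figure.** Section 2.11 gives changes of 10.49 ± 4.55 and 10.24 ± 4.46, 90% power, alpha 0.05, and 84 per group. The difference is 0.25 and the pooled SD is √((4.55² + 4.46²)/2) = 4.505. The article prints no margin and no sidedness, so 84 cannot be derived from stated inputs alone. Assuming a 2.0-point margin and one-sided alpha of 0.025, n = 2 × 4.505² × (1.960 + 1.282)² / (2.0 + 0.25)² ≈ 84.3, rounded up to 85, close to the stated 84. Allowing for dropout, 84/0.8 = 105 against the stated 104. Only HAMD-17 enters this calculation.

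**Count of primary variables** (sections 2.9 and 2.13.1), each scale counted once:
- Regions not tested separately: 2 + 8 + 10 = 20.
- Three regions (two dorsolateral, one cingulate): 2 + 8×3 + 10 = 36.
- Four regions (both areas bilateral): 2 + 8×4 + 10 = 44.

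The text does not settle which applies.

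**Chance of at least one P<.05 if no arm difference exists, independent tests:** 1 − 0.95^k.
- k = 20: 64.2%, with 20 × 0.05 = 1.0 false positive expected.
- k = 36: 84.2%, with 1.8 expected.
- k = 44: 89.5%, with 2.2 expected.

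**Allowing for correlation.** The documents give no correlations, so these are assumptions. Correlated normal test statistics were simulated (100,000 runs, two-sided 0.05). In the block version, correlation exists only within the scales (fixed at 0.6), within spectroscopy and within serum.

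| Structure | Correlation | k = 20 | k = 36 | k = 44 |
|---|---|---|---|---|
| Common to all | 0.3 | 54% | 71% | 77% |
| Common to all | 0.5 | 42% | 55% | 59% |
| Common to all | 0.7 | 29% | 37% | 39% |
| Within blocks | 0.3 | 59% | 76% | 81% |
| Within blocks | 0.5 | 51% | 65% | 69% |
| Within blocks | 0.7 | 42% | 51% | 53% |

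**Where the inflation sits** (independent tests).
- Markers only, k = 34 or 42: 82.5% or 88.4%.
- Ten serum markers alone: 1 − 0.95^10 = 40%.
- The two scales: 1 − 0.95² = 9.75%, and never above 2 × 0.05 = 10% whatever their correlation.

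**The case against.** The strongest defence is that efficacy and mechanism are different questions. The Introduction names both as primary objectives, section 2.1 calls the trial noninferiority, and section 2.11 uses HAMD-17 as the efficacy indicator. A significant cytokine would not show noninferiority on depression, so pooling all tests into one error rate overstates the risk to the efficacy conclusion. This stands: the efficacy pair carries at most about 10%, and the large figures belong to the mechanism claim. It does not remove the problem, because the marker family alone reaches 82% to 88% under independence.

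A second objection is that independence is the least plausible assumption. The ratios share metabolites with other listed outcomes, and markers may move together. This also stands and is why the correlated range is given.

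A third is direction. If the tests are two-sided, half of chance findings favour fluoxetine; the independent-test chance of at least one favouring acupuncture is 1 − 0.975^36 = 60% to 1 − 0.975^44 = 67%. That is a fair qualification for an acupuncture benefit claim, though a mechanism claim could use either direction.

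Finally, testing order and adjustment are often left to an analysis plan. That is accepted. The point rests on the stated primary list, the stated threshold and their mismatch with the sizing.

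**Conclusion.** The point holds. The article labels 20 measures, or 36 to 44 variables by region, as primary, each judged at P<.05, with only HAMD-17 change sized. If no arm difference exists, a chance-significant primary result is likely: 64% (20 tests) or 84% to 90% (36 to 44) under independence. Under the assumed correlations of 0.3 to 0.7 it is 29% to 59% for 20 tests and 37% to 81% for 36 to 44. Even the lowest of these is more than five times the nominal 5%.

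A reader might infer that a false positive is almost certain. The documents do not support that: even the highest figure needs every null to be true, all tests to be independent, and each region to be tested separately, which section 2.13.1 does not say. Nor do they support the inference that the efficacy conclusion carries an error of this size. For efficacy the defect is narrower: two co-listed scales, at most about 10%, and no rule if they disagree.

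**What to change.** By a dated, justified amendment made before the data are analysed by group:

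1. Name HAMD-17 change from baseline to end of treatment as the single primary outcome. Week 12 is inferred here, since section 2.11 says only that change before and after treatment was used; the amendment should state the time point.
2. Define success by the noninferiority comparison the trial was sized for, with its margin quoted, rather than by the test of difference in section 2.13.1.
3. Make SDS a key secondary outcome, tested only if that comparison succeeds.
4. Move the spectroscopy and serum markers to secondary or mechanistic outcomes, state which regions are tested, and set a multiplicity control within each family (Benjamini-Hochberg is one option). State that they carry no confirmatory efficacy claim.

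This needs no extra patients or measurements. The price is that mechanism results lose their primary label and some will become non-significant after adjustment. The change also comes late: section 2.6 puts conduct from May 2016 and the end of follow-up in the second half of 2019, and the trial is single-blind, so the amendment should record its date and that no comparison by group had been seen.
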